## Abstract

**Background:**

Deworming programs aimed at reducing morbidity and mortality from geohelminth infections are common in many countries where these infections are endemic, but data demonstrating increasing levels of resistance to albendazole and mebendazole are causes for concern. Studies to evaluate the clinical efficacy of deworming programs are critical to maintain high infection control goals.

**Methods:**

We propose to assess the clinical efficacy of Peruvian national guidelines for deworming programs in a prospective observational study conducted in the Amazon River basin area near Iquitos, Peru. Major outcomes to be evaluated include (1) albendazole resistance of intestinal helminths (trichuriasis, ascariasis, hookworm), and (2) frequency of reinfection with intestinal helminths 4 months after treatment with albendazole. Children ages 2–11 years from the Belén District of Iquitos will be identified based on a community census. Following parental informed consent, demographic data, weight, and height will be recorded and a stool specimen for parasitological exam by direct observation and Kato-Katz concentration method, and helminthic egg counts will be collected prior to administration of albendazole, following Peruvian national guidelines. Follow-up stool specimens examined in the same manner will be collected at 20 days, 90 days, and 100 days following initial administration of albendazole, and based on parasites found repeat treatment will be administered in accordance with national guidelines. Real-time multiplex qPCR will be performed on helminth positive samples collected prior to initial deworming and on helminth-positive specimens detected on day 15–20. A total sample size of 380 participants was calculated based on total population in the target group and prevalence estimates of helminth infections and clinical resistance based on recent data.

**Discussion:**

Data from observational clinical efficacy studies are important to guide geohelminth infection control programs.

*Trial registration*
https://www.researchregistry.com/. Identification number: researchregistry7736; Registered retrospectively March 13, 2022; https://www.researchregistry.com/browse-the-registry#home/registrationdetails/622e024cf06132001e3327bf/

## Background

Worldwide, approximately 1.5 billion people or about 24% of the world’s population, are infected with soil-transmitted helminths (STH) [1]. Soil-transmitted helminth infections are widely distributed in tropical and subtropical areas, especially in sub-Saharan Africa, America, China and East Asia. More than 267 million preschool-age children and more than 568 million school-age children live in areas with intense transmission and are able to benefit from treatment and prevention strategies [2]. In low- and middle-income countries, risk factors for STH infections include poverty and malnutrition, and STH infections have been associated with delays in cognitive, motor, and social development in children under 5 years of age [3, 4]. The presence of helminths also may cause intestinal blood loss with iron deficiency that manifests as anemia, especially in children with hookworm infection [5].

The World Health Organization and the Pan American Health Organization (WHO/PAHO) set standards for the control of soil-transmitted helminthiasis in Latin America and the Caribbean. These organizations recommend deworming strategies such as preventive chemotherapy (PC), which is an important part of a comprehensive package to eliminate morbidity due to soil-transmitted helminths in populations at risk. This strategy is applied according to the prevalence of soil-transmitted helminths in high-risk areas for preschool-age children (1 to 4 years) and school-age children (5 to 14 years) [6]. In high-risk areas with a prevalence of > 50%, the recommendation is for treatment twice a year (every 6 months), while in low-risk areas with a prevalence > 20 to < 50%, once a year (every 12 months) treatment with albendazole (400 mg) or mebendazole (500 mg) is recommended. In Peru, a universal dose is administered to children between 2 and 11 years of age twice a year in primary care health centers [7].

The efficacy of albendazole is variable against *Trichuris trichiura* compared to other anthelmintics; the cure rate ranges between 2.6 and 64.5% [8] and the egg reduction rate ranges between 7 and 83.1%. However, high cure rates of *Trichuris trichiura* are observed in some contexts [9–11]. In a study conducted in the Peruvian Amazon, an open-pair randomized trial was conducted in fifth-grade children from 18 primary schools (9 intervention and 9 control). Intensity of *Ascaris lumbricoides* infection at follow-up was 58% lower in children from intervention schools, a significant reduction as compared to children from control schools (RR = 0.42; 95% CI 0.21 to 0.85), but no significant changes were observed in the intensity of hookworm or *Trichuris trichiura* [12]. In another study from Peru, a total of 1193 school-age children were dewormed with a single dose of Albendazole (400 mg). Of the 909 children who tested positive for at least one STH infection, a random sample of 385 were followed up 2 weeks later with a second stool sample. The efficacy of albendazole was variable, with an egg reduction rate of 99.8% for *Ascaris lumbricoides* (95% CI 99.3–100); 93.6% for hookworm (95% CI 88.2–96.6), and 72.7% for *Trichuris trichiura* (95% CI 58.5–79, 1) [13]. In many cases treatment with albendazole alone appeared inadequate, especially for *Trichuris trichiura*. Other interventions such as combined therapy have been evaluated in other contexts. Ivermectin results in higher cure rates than albendazole and is well tolerated. The benefits of ivermectin for helminth infections would depend on the amount of resistance present [14–16].

Large-scale interventions to control soil-transmitted helminth infections at the community level with anthelmintic drugs such as albendazole have the potential to exert selective pressures which may favor the development of drug resistance, which could significantly reduce the benefits provided by deworming programs. Drug resistance in parasitic nematodes is caused by a single nucleotide polymorphism (SNP) in the β-tubulin gene at codon positions 200 (T → A), 167 (T → A) or 198 (A → C) [17].

Herein we describe the protocol for our observational study of a prospectively enrolled cohort to assess clinical resistance to albendazole and reinfection by intestinal helminths in children from the Peruvian Amazon receiving treatment according to Peruvian Ministry of Health treatment guidelines [7], to measure preventive treatment effectiveness for 6 months.

### Study design (see Fig. 1)

**Fig. 1 Fig1:**
[figure not shown]
Study design

Prospective cohort study of children aged 2 to 11 years, with an individual time of participation of 4 and a half months.

Participants will be boys and girls ages 2 to 11 years who live in the catchment area of the Centro de Salud 6 de Octubre, located in the district of Belén, city of Iquitos, and department of Loreto in Peru.

Inclusion criteria:Parental written informed consent, in addition to the verbal and written assent for children ages 6 to 11 years.No antiparasitic treatment in the prior 3 months [18].Permanent residence in the study community, with no plans to move in the next 6 months.

Major outcomes:Albendazole resistance of intestinal helminths (Trichuriasis, Ascariasis, Hookworm, Strongyloides).Reinfection with intestinal helminths 4 months after treatment with Albendazole.

### Sample size

Sampling will be carried out throughout the jurisdiction of the 6 de Octubre Health Center, which includes rural, peri-urban and urban areas, with a total potential study population of 3379 children ages 2 to 11 years based on health center databases. Based on this study population of 3379 children aged 2 to 11 years, to measure clinical resistance to albendazole a sample of 380 children was needed. This calculation was made in Epi Info Version 7.2 applying a type I error of 5% and assuming 50% prevalence of helminths in children, 25% frequency of *Trichuris trichiura* in children with helminths, 50% resistance to albendazole based on detection of any helminth in a follow-up sample and adjusting for 10% loss to follow-up for study participants.

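### The 380 children said to be needed to measure resistance come with no stated margin and best fit a proportion among all children; on the protocol's own assumptions about 171 infected children, 43 with Trichuris, would inform resistance

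*Protocol article*

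**What the plan says.** The Sample size section of the protocol article ties the number to a purpose: "to measure clinical resistance to albendazole a sample of 380 children was needed". It names the source population ("Based on this study population of 3379 children aged 2 to 11 years") and the software ("This calculation was made in Epi Info Version 7.2"), with a 5% type I error. The listed assumptions are:

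- Infection: half of all children (50%) carry a helminth.
- Trichuris: one in four infected children (25%) has this species.
- Resistance, which is worded as "50% resistance to albendazole based on detection of any helminth in a follow-up sample".
- Loss: one participant in ten (10%) is not followed up.

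No margin of precision is given, and the section does not show how the three percentages combine to give 380. The Abstract also bases the 380 on the total population of the target group and on prevalence and resistance estimates.

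Two other sections bear on this. Recruitment of participants sets a quota for each year of age. Statistical analysis limits the cure-rate calculation to children positive before the first dose and puts pretreatment positives in its denominator. Albendazole resistance is the first of the two major outcomes under Study design.

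**The concern.** A child with no worms before treatment cannot show that treatment failed to clear them. A sample sized for resistance should therefore either be scaled up for the share of children who are infected or state the precision expected in that smaller group. The section lists the fractions needed for this, but the total looks like a survey sample for one proportion among all children.

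At stake is how the first major outcome is read. Someone who takes 380 as the number that informs resistance would expect much tighter estimates than the study can give. The gap is widest for Trichuris, the species for which the Background says albendazole alone most often appeared inadequate.

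**Working it through.** **Inputs.** From Sample size: N = 3379, helminth prevalence 50%, Trichuris share of infected children 25%, resistance 50%, loss 10%, type I error 5% (taken as a two-sided 95% interval, z = 1.96). From Recruitment of participants: the age quotas. The margin d is not stated; ±5 points is an assumption, chosen because it recovers the plan's figure.

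**Reproducing 380.** For one proportion in a finite population:

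n = N·p(1−p) / [(d²/z²)(N−1) + p(1−p)]

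With N = 3379, p = 0.50 and d = 0.05:

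n = 844.75 / (2.198 + 0.25) = 345.0

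345.0 × 1.10 = 379.5, which rounds to 380. (Dividing by 0.90 would give 384, a small difference.)

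**Second match.** The quotas sum to 36+36+36+32+33+34+35+36+33+34 = 345, exactly the figure before the loss allowance.

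**Same margin, infected children only.**

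- All infected: N = 3379 × 0.5 ≈ 1690 gives about 313; × 1.10 = 344.
- Trichuris: N = 3379 × 0.125 ≈ 422 gives about 201; × 1.10 ≈ 221.

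Neither is 380.

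**Other margins, infected children.**

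- ±7.5 points, no finite-population correction: 1.96² × 0.25 / 0.075² = 170.7; / 0.5 / 0.9 = 379.4.
- ±15 points for Trichuris, no correction: 42.7 / 0.125 / 0.9 = 379.4.
- ±7.5 points, with correction (N ≈ 1690): 155.2 / 0.5 / 0.9 = 344.8.

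The first two reach 380 but do not use N = 3379, and their total before loss is about 342, not 345. The third uses N and reaches 345, but with the loss already included, so it does not lead to 380.

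**Evaluable children on the plan's own assumptions.** Half-width = 1.96 × √(0.25/n). The corrected value multiplies this by √[(N−n)/(N−1)], with N ≈ 1690 for infected children and 422 for Trichuris.

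| Enrolled | Followed (×0.9) | Group | n | Half-width, uncorrected | Half-width, corrected |
|---|---|---|---|---|---|
| 380 | 342 | Infected (×0.5) | 171 | ±7.5 | ±7.1 |
| 380 | 342 | Trichuris (×0.125) | 42.75 ≈ 43 | ±15.0 | ±14.2 |
| 345 | 310.5 | Infected | 155 | ±7.9 | ±7.5 |
| 345 | 310.5 | Trichuris | 39 | ±15.7 | ±15.0 |

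**Sensitivity to prevalence, 380 enrolled, uncorrected.** If 30% to 70% of children are infected, the evaluable counts run from 103 to 239 infected (±9.7 to ±6.3 points) and from 26 to 60 with Trichuris (±19.4 to ±12.7 points).

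**The case against.** **The margin is inferred.** The article states none, and a condensed article may leave it to the full protocol. A reader might infer that the study promises ±5 points for resistance and falls short, by reference to the roughly 698 children (with correction; 856 without) that ±5 among infected children would need. The documents do not support that charge, because they make no precision claim. The evaluable counts and half-widths in the table do not depend on the inferred margin.

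**The whole-population route is not the only one.** A reader might also conclude that 380 can arise in no other way and that the infection fractions played no part. Neither is established: ±7.5 points among infected children also gives 379.4. Prevalence and resistance are both set at 50%, so one cannot tell which of them was entered as the proportion. The whole-population reading is preferred because it uses the cited N and yields both 345 and 380. No single infected-children route examined that uses N does so. That makes it the better fit, not proof.

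**Resistance is not always tied to baseline infection.** The Sample size wording speaks of "50% resistance to albendazole based on detection of any helminth in a follow-up sample", Laboratory analysis equates a helminth-positive second sample with clinical resistance, and some samples negative at Day 0 but positive at Day 15 go to qPCR. This stands as a reason to fix the denominator explicitly. It does not rescue the calculation: counted over all children and ignoring new infections, the expected proportion would be 0.5 × 0.5 = 25%, which at ±5 points needs about 266, or 292 with the loss allowance.

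**Conclusion.** The point holds as a mismatch between the number and its stated purpose. The article presents 380 as the requirement for measuring resistance without a margin. The figure is best explained by one proportion among all 3379 children, with no scaling for the infected fraction. The cure-rate rule in Statistical analysis points to a baseline-positive denominator.

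Under the plan's assumptions, resistance would rest on about 171 children (±7.5 points, or ±7.1 corrected). Trichuris resistance would rest on about 43 (±15, or ±14.2 corrected), so an observed 50% would carry an interval of roughly 35% to 65%. Enrolling only the quota total lowers these to about 155 and 39.

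The counts rest on 50% prevalence, a 25% Trichuris share, 10% loss, and a denominator of children infected at Day 0. How 380 was actually derived remains an inference. The study is not invalid; its justification needs restating.

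**What to change.** Keep the enrolment and revise the text:

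1. State the margin of precision and the denominator actually used for 380.
2. Reconcile the quota total of 345 with the target of 380.
3. If the whole-population calculation is confirmed, say that it supports a proportion among all children, not resistance: 345 evaluable gives ±5.0 points with correction. The full 380, with no loss, would give about ±4.7.
4. Define the denominator for resistance to each species as children positive for that species at Day 0.
5. Give the expected evaluable numbers and 95% half-widths for resistance overall (about 171, ±7.5) and for Trichuris (about 43, ±15), say whether they include the finite-population correction, and recompute them if enrolment is 345.
6. Describe species-level resistance as descriptive, with exact confidence intervals.

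The cost is rewording, plus a stated precision for resistance that is less favourable than 380 suggests.

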### Laboratory analysis

Fecal samples will be analyzed by direct observation of eggs and/or larvae by microscopy and egg counting by the Kato-Katz technique. Direct microscopy is the diagnostic standard in areas with limited resources. The Kato-Katz method is used to estimate the intensity of infection by *Ascaris lumbricoides*, hookworms and *Trichuris trichiura*. Although this method is more sensitive than direct microscopy, it requires more time and labor to detect geohelminth eggs [25, 26]. Once the procedures have been carried out and the results obtained, the remaining stool samples will be aliquoted and stored at − 80 °C.

In the second sample, molecular detection of helminths by polymerase chain reaction (qPCR) will be performed on specimens with helminths detected (i.e., clinical resistance) in order to determine the presence of resistance markers at the genetic level.

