Direct observation: In a properly labeled slide, 0.5 g of feces will be applied with a wooden applicator and 20 µL of saline solution will be added. The first observation will be made from left to right, then the procedure will be repeated with 20 µL of Lugol’s solution added. Both observations will be made with the 10× and 40× objectives in order to qualitatively identify the absence or presence of helminths (*Ascaris lumbricoides*, *Trichuris trichiura*, hookworms, and *Strongyloides stercoralis*).Kato-Katz method: Two grams of feces will be placed on a smooth and sterile surface, covered with a piece of nylon and pressed with a flat-edge plastic applicator. The filtered feces will then be placed in the center of a 41.7 mg template on a slide until the hole is filled, after which the template will be removed and the sample will be covered with a cellophane sheet previously imbued in a glycerol-blue solution of methylene, and pressure will be applied until the sample is distributed homogeneously. After a 30-min incubation, eggs counts will be carried out using the 10× objective and a cell counter, the total number of eggs counts per species will be reported in eggs per gram (epg) and will be multiplied by 24 (41.7 mg template) [27], and the results of each parasite found will be recorded and reported quantitatively. This procedure will be performed on the 4 samples per subject collected throughout the study [28].STH infection by qPCR: To measure the intensity of the infection, quantitative polymerase chain reaction (qPCR) will be used in such a way that the Kato-Katz variability between users is reduced and the sensitivity of the detection of low-grade parasitic infections is increased [29, 30]. Real-time multiplex qPCR will be performed on positive samples (Day 0) for helminths that were identified by direct observation and Kato-Katz for the simultaneous detection of *Ascaris lumbricoides*, *Trichuris trichiura*, *Necator americanus*, *Ancylostoma duodenale*, and *Strongyloides stercoralis* [31]. If the sample from Day 0 is negative, the sample from Day 15 will be analyzed if it is positive for helminths. Amplification will be performed in a Quant Studio 7 Flex thermocycler (Applied biosystems) in a total volume of 25 µL using GoTaq® qPCR Probe Master Mix (Promega, USA) and 5 µL of fecal DNA. There will be two multiplex qPCR assays (STH1 and STH2); STH1 will be used to detect *Ascaris lumbricoides*, *Trichuris trichiura* and *Strongyloides stercoralis*, while STH2 will be used for the 3 species of hookworms. The cycling conditions for both cases will be the following: 1 cycle at 95 °C for 5 min, 40 cycles at 95 °C for 10 s and 1 cycle at 60 °C for 60 s. The primers will be the same ones used by Azzopardi et al. [32] which can be seen in Table 1.**Table 1 Tab1:** Primers used in multiplex qPCR analysis of stool samples by STH1 and STH2

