### Statistical analysis

Data will be analyzed in Access using Stata, using chi square, Fisher’s exact, and Wilcoxon tests to compare frequencies between groups. To analyze the data from direct observation and quantification by the Kato-Katz method, descriptive statistics will be used, to report the prevalence found in percentages. For the sociodemographic and clinical data of the study population, measures of central tendency and dispersion will be used for the quantitative variables and measures of relative frequency for the qualitative variables. Comparisons will also be made between sample 1, sample 2, sample 3 and sample 4 to determine the positivity of each species of parasite found using the Yates chi-square test, setting a significance level of p < 0.05.

The sociodemographic variables will be compared with the parasite load and presence/absence of parasites, using a multiple logistic regression model (univariate t-test), to determine the variables statistically associated with infection by *Ascaris lumbricoides*, *Trichuris trichiura* and hookworms.

The quantification performed with the Kato-Katz method will be compared with the Ct value (Ct threshold) of the multiplex qPCR, by converting Log10 of the absolute egg count per stool sample, in order to estimate the absolute egg counts in eggs per gram (EPG) in the DNA extractions, using the following formula [33]:$${\text{EPG}}\;{\text{Ascaris}} = 10\left( {{\text{Ct}} - 36.97} \right)/ - 3.489,$$$${\text{EPG}}\;{\text{Trichuris}} = 10\left( {{\text{Ct}} - 36.73} \right)/ - 3.288,$$$${\text{EPG}}\;N.\;americanus = 10\left( {{\text{Ct}} - 35.02} \right)/ - 3.641,$$$${\text{EPG}}\;A.\;duodenale = 10\left( {{\text{Ct}} - 35.02} \right)/ - 3.641.$$

To determine treatment efficacy, the prevalence will be measured before and after receiving treatment and compared using the Yates chi-square test. For calculations of cure rate and intensity of infection obtained from qPCR, only data from positive results before taking the first dose will be included [34].

The cure rate will be measured using the following formula:$$\frac{{\# \;{\text{positive}}\;{\text{for}}\;{\text{helminths}}\;\left( {{\text{pretreatment}}} \right) - \# \;{\text{negative}}\;{\text{for}}\;{\text{helminths}}\;\left( {{\text{post}}\;{\text{treatment}}} \right)}}{{\# \;{\text{cases}}\;{\text{positive}}\;{\text{for}}\;{\text{helminths}}\;\left( {{\text{pretreatment}}} \right)}} \times 100.$$

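### Clinical resistance is scored as any helminth at follow-up, without the same species at day 0, so the first major outcome can count infections that are not shown to be albendazole failures

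*Protocol article*

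**What the plan says.** The first major outcome, under Study design, is albendazole resistance, listed by helminth. The working rule appears in two other places. Sample size assumes "50% resistance to albendazole based on detection of any helminth in a follow-up sample". Laboratory analysis then selects second-sample "specimens with helminths detected (i.e., clinical resistance) in order to determine the presence of resistance markers at the genetic level".

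Four other statements bear on how the rule works:

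- The qPCR paragraph provides for children who are negative first and positive later: "If the sample from Day 0 is negative, the sample from Day 15 will be analyzed if it is positive for helminths".
- The treatment and follow-up section says that resistance and reinfection are both measured at 15–25, 90–100 and 130–140 days.
- Statistical analysis limits the cure rate and the qPCR intensity to baseline positives ("only data from positive results before taking the first dose will be included") and plans an egg reduction rate for each species. Neither is connected to the resistance outcome.
- The Background says of albendazole against Trichuris that "the cure rate ranges between 2.6 and 64.5" percent.

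**The concern.** A positive stool after treatment is evidence about albendazole only if the same species was there before the dose. The stated rule has no such condition. It therefore pools persistence, a change of species, infection not seen at day 0 and, at the later visits, reinfection, which is the study's second major outcome.

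The rule also treats every non-cure as resistance. For Trichuris, frequent non-cure after a single dose is already documented in the article's own Background, so a positive follow-up stool does not by itself indicate reduced susceptibility. A programme reading the result could not tell a change in drug response from efficacy that was already low.

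The qPCR step does not settle this. The helminth targets in Table 1 are 18S and internal transcribed spacer regions, whereas the Background places the resistance polymorphisms in the β-tubulin gene.

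**Working it through.** **1. The plan's own figure.** Inputs from Sample size: N = 3379, p = 0.50, type I error 5%, loss 10%. The margin is not stated; I assume d = 0.05.

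- n0 = 1.96² × 0.5 × 0.5 / 0.05² = 384
- n = 384 / (1 + 383/3379) = 345
- 345 × 1.10 = 379.5, or 380

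This reproduces the stated 380, and the age strata under Recruitment also sum to 345. The number is consistent with a proportion taken over all children, not over infected children.

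**2. Who the rule counts.**

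| Pattern | Counted as resistant? | What it shows about the first dose |
|---|---|---|
| Same species at day 0 and at 15–25 days | Yes | Treatment failure for that species |
| Negative at day 0, positive at 15–25 days | Yes | A missed infection that persisted, or a new one; cannot be told apart |
| Ascaris at day 0, only Trichuris at 15–25 days | Yes | Ascaris was cleared; Trichuris was not seen before the dose |
| Negative at 15–25 days, positive at a later visit | Can be, under the Sample size wording | Compatible with reinfection |

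In the second row, day-0 qPCR does not help, because it is run only on day-0 samples already positive by microscopy.

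**3. Trichuris non-cure.** Retained children: 380 × 0.9 = 342. Infected: 342 × 0.50 = 171. With Trichuris: 171 × 0.25 = 42.75, about 43.

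- Non-cure: 100 − 64.5 = 35.5% to 100 − 2.6 = 97.4%
- Children: 42.75 × 0.355 ≈ 15 to 42.75 × 0.974 ≈ 42

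These children would be called resistant at cure rates already reported elsewhere.

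**4. Precision under a baseline-positive definition.** 95% half-width at p = 0.50 is 1.96 × √(0.25/n).

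- Any helminth, n = 171: 7.5 points
- Trichuris, n = 42.75: 15.0 points
- All 342 children, with finite population correction: 5.0 points

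**The case against.** The Sample size phrase is a planning input, and the other phrase is a parenthesis in a rule for choosing specimens. The article is condensed, so a full definition may exist elsewhere. The major outcome is listed by helminth, positivity is to be compared by species across the four samples, the cure rate has pretreatment positives as its denominator, and egg reduction is planned by species. The sentence on day-0-negative children says which sample is assayed; it does not classify those children.

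Much of this stands: the data collected would support a correct analysis. But the two places that say what resistance means agree with each other and omit the day-0 and species conditions. The better measures are never tied to the outcome, and the cure-rate formula counts helminths, not species.

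Three stronger readings are tempting, and the documents do not support them.

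- *A reader might infer that a share 1 − s of resistant children is misclassified when microscopy has sensitivity s.* Take s = 0.8 at both visits, independent detection, 50% persistence and no new infection (all assumed). Then 171 observed positives imply 171/0.8 ≈ 214 infected and 43 missed. At follow-up, 171 × 0.5 × 0.8 ≈ 68 day-0-positive and 43 × 0.5 × 0.8 ≈ 17 day-0-negative children are found, and 17/85 = 20%. Yet those 17 were infected, treated and not cured. Here 85/171 = 49.7% is close to the true 50%, while requiring day-0 positivity gives 68/171 = 39.8%. The 20% does not measure error, and the documents give no sensitivity.
- *A reader might infer that a high resistance figure would appear whatever the true efficacy.* The 35.5–97.4% range is for Trichuris only. At a 25% share it contributes 0.25 × 35.5 = 8.9% to 0.25 × 97.4 = 24.4% of infected children. The rest depends on other species, with earlier Peruvian egg reduction rates of 99.8% (Ascaris) and 93.6% (hookworm). The Background also notes high Trichuris cure rates in some settings. The figure would move with real efficacy.
- *A reader might see the species lists as part of the defect.* Strongyloides is in the Study design outcome and not in the Abstract. That is an editorial mismatch.

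**Conclusion.** The concern holds as a defect in the outcome definition. The stated rule lets children who are negative at day 0, positive for a different species, or reinfected be counted as albendazole-resistant, and it gives the same label to Trichuris non-cure that the Background leads one to expect.

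The only part whose size can be taken from the documents is the last: 35.5–97.4% of Trichuris infections, about 15 to 42 of some 43 children. This rests on the plan's assumed 50% prevalence, 25% Trichuris share and 10% loss, and on the cited cure-rate range applying here. The number of day-0-negative, changed-species or reinfected children cannot be derived from the documents. The sample size of 380 is not shown to be wrong on its own inputs.

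**What to change.** - Define the first major outcome for each species as treatment failure at 15–25 days: the same species found at day 0 and at that visit, among children positive for that species at day 0.
- Report children negative at day 0 and positive at follow-up separately. Keep positivity first seen at the later visits under the reinfection outcome.
- Base any statement about reduced efficacy on the species egg reduction rate with a 95% CI, set beside the earlier Peruvian rates in the Background (Ascaris 99.8%, hookworm 93.6%, Trichuris 72.7%). None is given there for Strongyloides, so the plan should say that no comparator is available.

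The change is to wording and analysis; the stool data are already planned for collection. The cost is smaller denominators: about 171 children for any helminth and 43 for Trichuris, with the half-widths shown above. The plan should state that precision. It should also note that, if microscopy misses infections at follow-up, the failure rate among day-0 positives will be understated, as in the 39.8% example.

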### Recruitment of participants

To identify eligible children for the study, a community census is being conducted in the catchment area of the Centro de Salud 6 de Octubre, which includes rural, peri-urban and urban areas. Rural areas are defined as streets located on the opposite side of the Itaya river from the city of Iquitos, which is a flood prone area without basic services, electricity and drinking water. Peri-urban areas are located on the Iquitos side of the river and extend into the river, with houses on stilts or raft houses that float on the surface of the river. Many of these houses already have electricity and drinking water, and they are usually located around the health center. Another part of the study community is located in the urban area of Iquitos, with concrete houses that all basic services and access to food markets, etc.

For enrollment in rural areas, a sweep strategy will be applied, meaning that we will look for children who meet the inclusion criteria throughout the community. For the peri-urban area homes without an address (located on rafts) we will also apply the same strategy. In the peri-urban and urban area where there are well-defined maps with streets and addresses, we will recruit candidates with numerical codes from the community census based on a random number generator, starting from the first block and then moving forward clockwise to the next block.

Once the first randomly selected child of any age between 2 and 11 years has been recruited, enrollment will continue in the same way until the established strata are completed: age 2 years = 36 children; 3 years = 36 children; 4 years = 36; 5 years = 32 children; 6 years = 33 children; 7 years = 34 children; 8 years = 35 children; 9 years = 36 children; 10 years = 33 children; 11 years = 34 children. Once all the blocks of the study community have been sampled, if the target number of participants for each stratum were not completed, the process will be repeated from the beginning and thus complete the corresponding sample for each age group.

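### The 380 children appear to come from adding 10% to an inferred base of 345, and on that base they cover 9.2% loss, not the stated 10%

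*Protocol article*

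**What the plan says.** The Sample size section of the protocol article states that "to measure clinical resistance to albendazole a sample of 380 children was needed". The inputs it lists are:

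- the population: "Based on this study population of 3379 children aged 2 to 11 years";
- a type I error of 5%;
- helminth prevalence: "assuming 50% prevalence of helminths in children";
- a 25% share of *Trichuris trichiura* among infected children;
- resistance: "50% resistance to albendazole based on detection of any helminth in a follow-up sample";
- the loss allowance: "adjusting for 10% loss to follow-up for study participants".

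The section names Epi Info as the software. It prints no margin of error, no sample size before the loss allowance and no inflation formula. The abstract repeats the total of 380.

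Recruitment of participants sets enrolment quotas by year of age, beginning "age 2 years = 36 children; 3 years = 36 children; 4 years = 36; 5 years = 32 children; 6 years = 33 children" and continuing with 34, 35, 36, 33 and 34 for ages 7 to 11.

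**The concern.** A total said to be adjusted for 10% loss should leave the required number after 10% of those enrolled are lost. Loss acts on the enrolled number, so the base has to be divided by the retained fraction, 0.90. Adding 10% of the base gives a smaller total and falls slightly short. The stated total looks like the result of adding.

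What is at stake is whether the stated property of 380 is true. The quotas and the total already need to be reconciled. If that is done by scaling the quotas up to 380, the same small shortfall carries over into enrolment.

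**Working it through.** **Inputs from the documents.** N = 3379, p = 0.50, type I error 5% (z = 1.96), loss 10%, stated total 380 (Sample size); ten age quotas (Recruitment of participants).

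**Assumption.** A margin d of 5 percentage points. The documents give none.

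**Step 1: reproduce the base.** The survey formula for one proportion with finite-population correction is

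n = N p(1 - p) / [(d/z)² (N - 1) + p(1 - p)].

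Without the correction, n0 = 1.96² x 0.25 / 0.05² = 384.16. With it, n = 384.16 / (1 + 383.16/3379) = 345.0.

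**Step 2: compare with the quotas.** 36 + 36 + 36 + 32 + 33 = 173 and 34 + 35 + 36 + 33 + 34 = 172. The sum is 345, the same number reached by a separate route.

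**Step 3: reproduce the stated total.**

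| Inflation of 345 for 10% loss | Result | Rounded up |
|---|---|---|
| Add 10% of the base: 345 x 1.10 | 379.5 | 380 |
| Divide by the retained fraction: 345 / 0.90 | 383.3 | 384 |

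Only the first gives the printed figure.

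**Step 4: try other inputs.** With p = 0.5 and the correction, other margins give these totals:

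| Margin (points) | Base x 1.10 | Base / 0.90 |
|---|---|---|
| 3 | 892.1 | 901.1 |
| 4 | 561.0 | 566.7 |
| 6 | 271.7 | 274.4 |
| 7 | 203.5 | 205.6 |
| 10 | 102.3 | 103.3 |

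With a 5-point margin and p = 0.25, 0.125 or 0.0625, the total is at most about 295. Without the finite-population correction it is 424 (adding) or 428 (dividing). None of these gives 380.

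**Step 5: what 380 delivers.** 380 x 0.90 = 342, which is 345 - 342 = 3 below the base. The loss that 380 can absorb is (380 - 345)/380 = 9.2%.

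**Step 6: effect on precision.** The whole-population half-width is 1.96 x √[0.25/n x (3379 - n)/3378]. It is 5.00 points at n = 345 and 5.02 points (5.0246) at n = 342.

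**The case against.** The strongest objection is that the alleged error sits in a step the article does not print. The 5-point margin is supplied from outside, the reconstruction makes no use of the 25% *Trichuris* share, and the recruitment section presents 345 as enrolment quotas, not as a pre-loss requirement. One could also note that 342/0.90 = 380, so the total would be correctly inflated if the base were 342. This stands as a limit on certainty: the base is inferred. It does not remove the point. A base of 342 would need a planned margin of 5.02 points, which is not a natural planning value, and nothing in the article sums to 342. The conventional 5-point margin and the quotas both lead to 345.

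The second objection is size: three children in 345, against a loss rate that is itself a round guess. That stands too, and it is why this is a minor correction.

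A reader might infer more than the documents support:

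- *The article states a wrong inflation formula.* It states none; the formula is deduced from the total.
- *The study is materially undersized because of this step.* A change of 0.02 points in half-width does not support that.
- *342 evaluable children would give about 5-point precision for resistance.* That half-width applies to a proportion of all children sampled. Resistance concerns children who were infected, and the Statistical analysis section limits the cure rate to those positive before the first dose. At the assumed 50% prevalence, that is 342 x 0.50 = 171 children, with a half-width of 1.96 x √(0.25/171) = 7.5 points without finite-population correction.

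**Conclusion.** The point holds as a minor correction. On an inferred base of 345, the statement that 380 allows for 10% loss is not quite true: 380 leaves 342 after 10% loss and covers 9.2%. An exact allowance would need 384, which is 4 more children, or about 1%.

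This rests on two assumptions: a 5-point margin, and a base equal to the number that both the formula and the quotas give. No analysis or conclusion of the study turns on it.

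The mismatch between the quotas and the total has a larger effect. If enrolment stops at the quotas, there is no loss allowance at all: 10% loss leaves 345 x 0.90 = 310.5, about 310 children, with a whole-population half-width of about 5.3 points.

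**What to change.** In the Sample size section, state the base (345, if the authors confirm it) and the margin of error used. Then choose one of two options:

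- **Keep 380.** Say that it allows for about 9.2% loss, with 342 evaluable children if 10% are lost. This costs one sentence and no extra children.
- **Use 384 = 345/0.90.** This means 4 more children, and the total must also be changed in the abstract.

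In neither case attach the 5-point half-width to the resistance estimate, since that is made only in helminth-positive children.

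With either option, reconcile the age quotas under Recruitment of participants with the enrolment total. They now add up to 345, so they need 35 more places to reach 380 or 39 more to reach 384.
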